### Randomization

Randomization will take place on an individual level. Before providing informed consent, participants are fully informed about the trial’s randomization procedures. Following inclusion, i.e., between T0 and T1, participants will be randomized to one of 6 study arms (3 PrevOP-MMT * 2 PrevOP-PAP conditions, see Fig. 2), using computer-generated random numbers, stratified by gender. Randomization procedures take place outside the study center at the Institute for Clinical Epidemiology and Applied Biometry at Tübingen University Medical Center. PrevOP-PAP study staff are informed about participant allocation to intervention arms via fax by the end of the baseline phase.

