### Statistical analyses

#### Randomization check, manipulation check, drop-out analyses, and intention to treat

A randomization check will address equal distributions of all baseline measures of all outcomes and covariates across conditions using multivariate analyses of variance and chi-square tests for nominal and ordinal-scale baseline data. Manipulation checks of intervention strategies will test differential intra-individual increases of cognitive and social variables targeted with the different intervention modules. For this, 2-level mixed models with TIME as a within-subjects factor and condition (PrevOP-PAP-I; PrevOP-PAP-CTRL) as the between-subjects factor as well as their interaction will be fit.

Analyses will be carried out in an intention-to-treat manner. Depending on the analytical approach to the main hypotheses, multiple imputation or full information maximum likelihood strategies will be used to keep information of individuals who were randomized to one of the PAP conditions, but dropped out at any later point of the study, in the analyses. Drop-out analyses will test baseline differences between continuers and non-continuers in all variable groups using *t*-tests, chi-square tests, and logistic regressions. Identified unique differences between continuers and non-continuers (i.e., drop-out mechanisms) will be included in the imputation model (along with this study’s central variables; in case of multiple imputation) or path models (in case of full information maximum likelihood; [57]). Use of either is pre-determined by the statistical approach used to test our hypotheses.

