#### Hypotheses tests

Longitudinal mediation analyses will be conducted using manifest path analyses. PrevOP-PAP-condition will be specified as a dummy-coded independent variable, accelerometer-assessed MVPA as a mediator (in minutes per week), and WOMAC scores as the primary outcome (controlling for respective baseline assessment). Dummy-coded PrevOP-MMT-conditions will be routinely tested as moderators of the association between MVPA (mediator) and WOMAC (primary outcome). If no interactions occur, PrevOP-MMT-conditions are tested as simple-effect covariates and dropped only if they are not related to the mediator or primary outcome. Further covariates are determined by results of the randomization check and bivariate correlations of assumed covariates with primary or secondary outcomes. Significance of all indirect effects will be tested using bootstrapping methods.

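### Covariates beyond the baseline values are chosen by randomisation-check results and outcome correlations, so the primary model is not fixed and neither sex nor MMT arm is guaranteed a place in it

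*Protocol article*

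**What the plan says.** All references are to the protocol article.

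- **Hypotheses tests** sets up a path model with PAP condition as predictor, accelerometer-measured MVPA as mediator and "WOMAC scores as the primary outcome (controlling for respective baseline assessment". These elements are fixed in advance.
- MMT arm is first tested as a moderator of the path from MVPA to WOMAC. If there is no interaction, "PrevOP-MMT-conditions are tested as simple-effect covariates and dropped only if they are not related to the mediator or primary outcome".
- For everything else, "Further covariates are determined by results of the randomization check and bivariate correlations of assumed covariates with primary or secondary outcomes". Examining intervention mechanisms carries this rule over to the mechanism models.
- **Randomization check, manipulation check, drop-out analyses, and intention to treat** describes the check: "A randomization check will address equal distributions of all baseline measures of all outcomes and covariates across conditions using multivariate analyses of variance", with chi-square tests for nominal and ordinal measures. The same section adds predictors of drop-out to the imputation model or, under full information maximum likelihood, to the path models.
- **Randomization** allocates to six arms (3 MMT by 2 PAP), "using computer-generated random numbers, stratified by gender". Sex appears again only in the list of variables collected.
- **Masking** states that study staff analyse the data without masking.

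**The concern.** Under proper randomisation any baseline difference between arms is chance. A significance test of it does not show which variables need adjustment; that depends on how strongly a variable predicts the outcome. The second criterion, correlation with the outcomes, lets the trial's own data set the model. The article gives no time point for those correlations, so they may include values measured after randomisation.

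The two factors that belong in the model by design are the ones left conditional. Gender enters only if one of the screens selects it. MMT arm is a co-randomised exercise intervention that could plausibly act on both MVPA and WOMAC, yet it can be removed after a non-significant test, and such a test does not show absence of effect.

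At stake is whether a reader can tell which primary model was planned, given that the analysts know the allocation, and whether its standard error matches the design.

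**Working it through.** **1. The plan's own figure.** Power analysis gives f = 0.1, stability 0.68, 5 time points, 2 groups, alpha 0.05 and power 0.95. For the within-between interaction, lambda = f² × N × m / (1 − rho) = 0.01 × 122 × 5 / 0.32 = 19.06, with 4 and 480 df. Power is 0.953. N = 121 gives 0.952, and 122 is the first even number. For drop-out, 122 / 0.8 = 152.5, so 153. Both stated figures reproduce, and nothing below changes them.

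**2. Which terms are guaranteed.**

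| Term | Status in the text |
|---|---|
| PAP condition, MVPA, WOMAC | fixed |
| Respective baseline value | fixed |
| MMT arm | kept if an interaction is found, or if related to mediator or outcome; otherwise dropped |
| Gender (stratifier) | not named; enters only through a screen |
| Other covariates | randomisation check and outcome correlations |

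**3. How often a real MMT effect would fail a test on WOMAC.** Assume both exercise arms differ from the MMT control by 0.3 SD, so the arm means are 0, 0.3 and 0.3. The variance of the means is (0.2² + 0.1² + 0.1²) / 3 = 0.02. Take the protocol's stability of 0.68 as the correlation with baseline, so the residual variance is 1 − 0.68² = 0.5376. Then lambda = N × 0.02 / 0.5376, tested with 2 and N − 4 df at 5%.

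| N | lambda | critical F | power | missed |
|---|---|---|---|---|
| 192 (= 240 × 0.8) | 7.14 | 3.04 | 0.66 | 34% |
| 240 (no information lost) | 8.93 | 3.03 | 0.76 | 24% |

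A relation to MVPA would also keep MMT in the model, so the plan's own rule would drop it less often than this.

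**4. Effect on the treatment comparison.** Simulation with no PAP effect, 3,000 runs in each of four scenarios. All inputs are assumed: 192 completers, 20 candidate covariates plus gender, a 5% threshold, gender and MMT effects of 0.2 to 0.3 against a residual SD of 0.65, and arms balanced within gender. It uses linear regression of WOMAC on PAP arm, not the bootstrapped indirect effect, and screens MMT on WOMAC alone, so it overstates how often MMT is lost.

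- Gender was left out in 49% to 74% of trials, and MMT arm in 40% to 70%.
- Type I error was 4.1% to 4.9% with selection by either criterion, against 4.5% to 5.1% for a fixed model with baseline, MMT and gender.
- Taking the best of four readings of the rule (randomisation check, correlation, either, both) gave 5.7% to 6.8%.
- With baseline adjustment only, the mean standard error was 2% to 4% larger than in the fixed model (for example 0.1143 / 0.1104 = 1.035), while the true spread of the estimates was the same (0.1095 in both). The error is on the conservative side: rejection was 4.0% to 4.9%.

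A separate simulation with 40 or 50 pure-noise covariates gave type I error of 6.0% and 5.0% with selection, against 5.8% and 4.8% without.

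**The case against.** The strongest reply is that the rule does little harm, and much of that stands.

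- A reader might infer that the whole model is set by chance and outcome data. It is not. Condition, mediator, outcome and baseline values are fixed, and only further covariates are selected.
- A reader might infer that false positives are materially inflated. Under one rule applied mechanically they are not: the differences from a fixed model are about the size of simulation error. The 5.7% to 6.8% needs a choice among readings, which the article does not license, although its wording does not exclude it.
- A reader might take the miss rate for MMT as 60%. That comes from a WOMAC test without baseline adjustment (lambda = 192 × 0.02 = 3.84, power 0.395). The plan adjusts for baseline and also keeps MMT if it relates to MVPA.
- A reader might count false imbalances as independent 5% tests: 1 − 0.95^20 = 64% for 20 measures. The plan specifies multivariate analysis of variance for continuous measures, so that count does not describe it.
- Screening on outcomes can pick up prognostic variables. In the simulated scenarios that contained some, the selected model had a smaller standard error than the fixed one (for example 0.0992 against 0.1104). A strongly prognostic gender would tend to be selected, and a weak one costs little when omitted.

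A full analysis plan may define thresholds and how the two criteria combine, and their absence here is not the point. The selection rule itself is stated in the article. Naming prognostic covariates in advance obtains the same precision without letting the results choose them.

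**Conclusion.** The point holds as one of pre-specification and modest precision, not of validity. The article selects further covariates from tests of chance imbalance and from outcome correlations, allows a co-randomised factor to be dropped on a test, and commits the stratifier to no model, while the analysts are unmasked. The primary model is therefore not fixed.

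Type I error stays near 5% under any single mechanical rule. The cost is analyst discretion, together with lost precision and standard errors that are somewhat too large when the design factors are left out (2% to 4% in the simulated scenarios). A 0.3 SD exercise effect on WOMAC would be missed by a baseline-adjusted test 24% to 34% of the time, and less often under the plan's two-route rule. These sizes rest on the assumed effects, thresholds and covariate counts given above. The reading of the text does not. The change should be made, because it is nearly free.

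**What to change.** In Hypotheses tests and Examining intervention mechanisms:

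- Keep the respective baseline values, and add sex and the two MMT dummies as fixed terms whatever their p-values. Add the MMT-by-MVPA interaction if the planned moderator test calls for it.
- Name any other prognostic baseline covariates before any outcome data are analysed. Tying this to unmasking would not work, because the analysis is not masked.
- Remove the randomisation check and the outcome correlations as selection rules, and report baseline data descriptively by arm.
- Keep the drop-out predictors for missing-data handling only, in the imputation model or as auxiliary variables under full information maximum likelihood.

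The cost is analysis wording. Sex and MMT arm are already recorded, the sample size figures of 122 and 153 are unchanged, and recruitment was still under way when the article was submitted.

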#### Examining intervention mechanisms

To test the assumptions of the HAPA and its extensions with social network and social exchange indicators, path analyses are employed. PrevOP-PAP condition will be specified as a dummy-coded independent variable, proposed cognitive and social intervention mechanisms as mediators (controlling for respective baseline assessments), and accelerometer-assessed PA as the outcomes (controlling for respective baseline assessment). Beyond PrevOP-MMT-conditions, further covariates are determined as outlined above. Significance of all indirect effects will be tested.

#### Additional analyses

Additional 2-level mixed model analyses will be used to examine intra-individual change (within-person) in primary and secondary outcome variables as a function of study conditions (between-person). Analyses using available self-report PA data will benefit from a larger number of - and more tightly-spaced assessments.

### Dissemination plan

The trial registration and study protocol are the first publications of this RCT. This protocol complies with SPIRIT guidelines [58]. Findings of this RCT will be published in peer-reviewed international journals and at national and international conferences. Dissemination of results in journals will comply with CONSORT guidelines [59]. Additional dissemination to the public is planned at public institutional events and via various media (website, press).

## Discussion

Using a psychological adherence program that is based on the HAPA [16] presently extended to include proposed social predictors of behavior change [30], this RCT will contribute to a better understanding of the psychological and social mechanisms of the uptake and maintenance of physical activity and their relation to disease symptoms in persons with OAK.

As reviewed throughout this study protocol, the PrevOP-PAP and this RCT have a number of strengths. However, most of these feature accompanying risks. Both are reviewed next and the discussion is closed with limitations of the RCT and an outlook.

First, the PrevOP-PAP is based on theory and makes use of a number of defined and theoretically-derived behavior change techniques [13, 16]. Amongst other benefits, this theory-centered approach facilitates the examination of active ingredients of the intervention and the cumulation of findings associated with this specified set of behavior change predictors and techniques. Theory-based approaches can thus contribute to the development of economic yet effective intervention measures and provide specific testable predictions not only for the kind of predictors playing a role in behavior change, but also for their temporal alignment in the behavior change process [16]. This provides vital information on future improvements of interventions.

A strength of this RCT is its use of objective behavioral indicator operationalizations, i.e., objective PA. Objective measures avoid many of the problems associated with common method variance or recall biases. As such, examined associations are not inflated by the fact that they are all measured as self-reports [60] and with items that are framed in a behavior-specific way and thus all directly address the behavior in question (i.e., principle of compatibility; [61]). Thus, using an objective behavioral indicator one may also reduce to some extent mere measurement effects created by a cumulation of similar sounding items that are completed and may produce behavior change themselves [62]. Accelerometers used in this study feature an additional benefit as they do not have screens and thus do not feed back the amount of PA to participants. Data have to be downloaded and processed to gain this information. This might again reduce reactive measurement and does not induce an unwanted intervention component of action control in the assessments. Drawbacks associated with the use of accelerometers, however, are also present. First, despite of the advantages described above, there have been reports of early reactive assessment effects (pertaining to baselines) when accelerometers are used [63]. Additionally, hip-worn accelerometers cannot capture activity associated with a number of specific types of PA, such as those where hips stay fairly steady (e.g., riding a bike) [64]. Relatedly, using only accelerometers, one cannot assess the type of PA a person has practiced, only time spans of different intensities of PA during the day or basic step counts can be estimated. It is for this reason that we additionally assess PA via self-report which is fraught with all the faults that have already been reviewed above.

A further strength of the RCT is its fairly long follow-up period of 24 months with a sufficient time span without interventions (12 months) to examine longer-term effects of the PrevOP-PAP on the maintenance of regular PA. Moreover, several repeated assessments allow for testing mediation processes. Again, these benefits come with certain risks, such as a relatively high expected dropout over the two years or increased participant burden due to intense intervention regimens and several repeated assessments. A number of precautions against attrition are realized within the PrevOP trial [65]. For instance, there is an active control group, participants are regularly contacted and reminded of the remaining interventions and assessments, and appointments are scheduled upfront. Many of the assessments and intervention components of both the PrevOP-PAP and PrevOP-MMT are face to face, which may also increase participant commitment.

Furthermore, computer-assisted intervention sessions facilitate standardized delivery of intervention contents, but leave room for individual interaction and tailoring intervention contents and delivery to participants’ needs.

In addition to the strengths and risks reviewed above, this RCT also has a number of limitations. An important limitation is the lack of masking or blinding within the PrevOP-PAP-I. Due to ethical and practical reasons masking is not feasible in this trial. Participants are informed about the possibility to be randomly allocated to intervention or control conditions upon inclusion and study staff are aware of the treatment they deliver. Moreover, although the PAP-I includes a network-creation component and participants are asked about social exchange processes with their sports companions and/or close others, there are no data generated by these other persons. Thus, dyadic or group effects cannot be studied in a fully reciprocal manner in this study [66]. Additionally, except for the accelerometer and assessed medical data, this study largely relies on self-report measures that are subject to recall bias and mere measurement effects as reviewed above.

As an outlook, the design and evaluation of the theory-based PrevOP-PAP are intended to become a yardstick for future development and implementation of digitalized psychological adherence programs for this population. Depending on the (to be determined) efficacy of the PrevOP-PAP and for a partially or fully digitalized implementation of the program, next steps could include the examination of different delivery modes in a factorial RCT design. Study conditions might entail graded delivery modes using different shares of personal interaction with trained study personnel to test the efficacy of a fully digitalized version of the program.

### Protocol version and trial status

This is the original study protocol as registered with the German Clinical Trials Register on 26 January 2016. No protocol modifications are planned at this time. If future protocol modifications take place, they will be reported (e.g., in the trial registry and upon publication of study results). Recruitment started in February 2016 and was continuing when the protocol was submitted for publication.

## Abbreviations

BCT: Behavior Change Techniques
CONSORT: Consolidated Standards of Reporting Trials
HAPA: Health Action Process Approach
OAK: OsteoArthritis of the Knee
PA: Physical Activity
PAP: Psychological Adherence Program
PrevOP: PREVenting the impairment of primary Osteoarthritis by high impact long-term Physical exercise regimen
PrevOP-MMT: PrevOP-Main Medical Trial
PrevOP-MMT-CTRL: PrevOP-MMT ConTRoL condition
PrevOP-MMT-HIE: PrevOP-MMT High Impact long-term physical Exercise condition
PrevOP-MMT-LIE: PrevOP-MMT Low Impact long-term physical Exercise condition
PrevOP-PAP: PrevOP-Psychological Adherence Program
PrevOP-PAP-CTRL: PrevOP-PAP ConTRoL condition
PrevOP-PAP-I: PrevOP-PAP Intervention condition
RCT: Randomized Controlled Trial
SPIRIT: Standard Protocol Items: Recommendations for Interventional Trials
T: Time
WOMAC: Western Ontario and Mc MAster universities osteoarthritis index
